## Methods and Analysis

### Trial Design

The protocol presented herein reflects Protocol Number 01. Any amends to this protocol will be detailed in full within the ISRCTN registry. This observational cohort study will be conducted following the STROBE statement (25) for observational studies with the protocol reported in line with SPIRIT Statement (26). We will examine the effectiveness of a 12-week blended community rehabilitation programme on improvements in HR-QoL and reductions in symptoms of COVID-19, in individuals recovering from the disease.

This evaluation will be conducted in concert with the NHS. Initially the programme will be deployed across 4 NHS locations, namely; University Hospitals of North Midlands Trust, Newcastle upon Tyne Hospitals NHS Foundation Trust; Birmingham and Solihull Community Care Group and Central Manchester University Hospitals Trust. Whilst these locations are clustered in the North and Midlands they are demographically and economically diverse. The NHS sites will be serviced by 8 surrounding Nuffield Health Fitness and Well-being Centres, all of which are registered with the Care Quality Commission and are located within a 20-mile radius of a participating NHS site. Each trust will be assigned 2 rehabilitation specialists from Nuffield Health to support the programme. As this intervention will be offered as a National service, recruitment is open ended beginning in September 2020. Nuffield Health intend to expand provision by operationalising all 112 of its fitness and well-being centres in 2021. These locations cover all 7 geographical regions as defined by NHS criteria. An initial evaluation cohort will not exceed 160 participants ensuring that a participant practitioner ratio of 1:10 is not exceeded.

Those wishing to access the programme can do so via NHS referral, this can be through doctor, nurse or other allied health professional such as a physiotherapist. Patients will only be referred if they meet the qualifying criteria presented in Table 1.

**Table 1 T1:** Inclusion and exclusion criteria.

**Inclusion criteria**	**Exclusion criteria**
Previous diagnosis of COVID-19	Active COVID-19 symptoms
Able to walk independently for a minimum of 20 m	Are already receiving community rehabilitation
Must have access to the internet and smartphone/tablet/personal computer (with adequate technological literacy)	Have un-managed medical conditions that contraindicate unsupervised exercise
18 years of age and over	Have a formal diagnosis of post-traumatic stress syndrome, clinically significant anxiety or depression where low intensity mental health intervention will not assist
Access to transport for phase 2 attendance	Have been diagnosed with Chronic Fatigue Syndrome

Once referred, the patient will complete an online pre-assessment health questionnaire. Once completed the questionnaire is made available digitally to a specialist trained physiotherapist who will contact the patient to conduct a telephone triage assessment. Following successful triage, the patient is handed on to a rehabilitation specialist who then takes up responsibility of the patients care. All patients will receive the identical 12-week programme structure consisting of two 6-week phases, depicted in Figure 1 and described in detail below.

**Figure 1 F1:**
[figure not shown]
Pathway illustration of the 12-week community rehabilitation programme.

### Rehabilitation Programme

NHS healthcare professionals will utilise inclusion/exclusion criteria at the point of discharge to refer a patient to the programme. Alongside the provision of a patient information document, the patient will be fully informed verbally about the programme, being given the opportunity to join the programme should they so wish. The patient will be made aware that their data will be utilised anonymously for research purposes. The patient may also request that their data is not utilised and will still be able to participate in the programme. Should they choose not to progress they will be sign-posted to alternative community/NHS services where available. If the patient accepts to progress on to the programme the NHS healthcare professional will complete an online referral, sent directly to Nuffield Health using a secure online form. Data sharing agreements have been completed between NHS and Nuffield Health and all processes conform to GDPR and NHS digital requirements.When an online referral is completed, an automated booking process is triggered. Via email or telephone (based on patient preference) the patient will choose an appointment time for an initial triage screening. The patient will also be asked to complete pre-screening questions, designed to support the triage process.The patient next joins a telephone or online video triage consultation utilising this feature. The triage is conducted by specialist physiotherapists trained in remote consultation. The triage is designed to be an additional safety step ensuring that the patient is clinically fit to progress onto the 12-week programme. The 45-min triage will also act to collect additional relevant patient information that may be pertinent when tailoring their exercise programme. Information such as details on additional co-morbidities, emotional well-being and medication will be discussed. Should any contraindications to exercise be identified during the triage the patient will be informed that they are unable to progress on the programme at that time. The patient will be sign-posted back to their General Practitioner, who will also be notified in writing. The original referring clinician will also be notified. At the end of triage, if deemed appropriate, the specialist physiotherapist will refer the patient to the rehabilitation specialist with recommendations for the intensity of entry level exercise and specific needs and goals.Following successful triage, the patient will be automatically sent a welcome pack via post as well as email. This will provide full guidance on how to download, access and register on the digital platforms and will provide links to learning materials. The patients GP will also be made aware that their patient has initiated the programme. The digital application platform utilises the functionality of a platform already used extensively across Nuffield Health (MyTherapy, Nuffield Health, London, UK). All other virtual audio-visual communication will be delivered by a separate digital system (Microsoft Teams, Microsoft, Redmond, USA).Within 72 h of referral, the patient will be contacted by their assigned rehabilitation specialist based at a Nuffield Health site within a 20-mile proximity to the referring hospital. practitioner will provide a welcome to the programme, offer the opportunity to ask any questions and to inform them of the start date of the programme.The patient begins the 12-week programme. This programme phases are as follows:

### Phase 1

Weeks 1–6 will consist of 3 exercise sessions per week. Session 1 will be an online live streamed activity conducted by 2 Nuffield Health trained rehabilitation specialists. One practitioner will run the exercise session and the second will answer questions via the online chat function. The stream will be a 1-way stream, meaning that whilst multiple patients will access the stream at any given time, they will not be recorded/filmed nor will their personal details be visible to the group. A maximum of 10 patients will join a stream at any time. The live stream will last up to 45-min followed by a 15-min period for questions via the secure online chat function or alternatively spoken questions can be provided should the patient have microphone functionality.

The second session of the week during phase 1 will be self-directed. The patient will be directed to a pre-recorded guided exercise session located on a dedicated online platform (Vimeo, New York, USA). This will be a 45-min activity which the patient completes at their leisure. All exercises are designed such that they can be carried out with ease at home.

The third exercise session of the week is described as “build your own.” The patient's workbook provides the patient a menu of activities suitable for them, which they may select to populate an exercise session commensurate with their personal threshold.

Each week the patient will be provided a phone call that will last up to 45-min with the rehabilitation specialist. The aim of the phone call is to listen to any patient queries but to also offer support on themes such exercise selection, symptom management and emotional well-being. Nuffield Health specialists have comprehensive training in each of these areas. Prior to progressing to Phase 2 patients will receive a remote mid-point review by the rehabilitation specialist. Progress will be discussed in detail and the patient will be asked if they feel ready and willing to progress to phase 2. If their progress is deemed insufficient, the patient will be recommended to complete another 6-week digital programme in full, before moving into a gym-based setting. Progress will be reviewed weekly and patients will be able to join the face to face component at a later point. All group-based sessions will be offered at two time points across the course of the day, with an AM and PM option. All one to one activity such as the weekly phone calls will be booked according to participant preference on a weekly basis. All above processes intended to maximise participant retention throughout the course of the evaluation.

### Phase 2

Following successful completion of phase 1, patients will progress to the phase 2 face to face programme. This phase will be conducted in strictly controlled gym environments conforming to all necessary Government and Public Health England (PHE) guidance. As per phase 1, phase 2 will consist of 3 exercise sessions per week. The first session of the week will be a rehabilitation specialist lead group exercise programme. In appropriately prepared and ventilated spaces, groups of up to 5–10 patients will engage in a 45-min exercise class followed by 15 min for questions and answers. Exercises will consist of aerobic and strength-based exercises as well as stability and mobility. In order to promote continued self-management, the second exercise session of the week will be a remote pre-recorded session that the patient will carry out at home independently, as per phase 1. Similarly, the third session of the week, “build your own” will remain; however, the patient will be encouraged to complete this session within a supervised gym environment. The rehabilitation specialist will be on hand within pre-defined time slots to provide advice and guidance. The patient will again receive a weekly consultation with the rehabilitation specialist following the aforementioned themes. This will culminate between weeks 12 and 13 with a final assessment, summary report and sign-posting to additional services where required.

### Practitioner Recruitment and Training

Rehabilitation specialists will be recruited and trained from a pool of exercise professionals working within Nuffield Health. All exercise professionals have a foundation training to a minimum of The Level 3 Personal Training Qualification from an accredited training provider, with preference for professionals trained to level 4. The competencies associated with these qualifications can be found elsewhere. All professionals are registered with The Chartered Institute for the Management of Sport and Physical Activity (CIMSPA). As part of this registration, all professionals are required to engage in continued professional development (CPD) as part of their contract of employment, with a pre-requisite to attain a minimum of 10 CPD points each year. Given the unique structure of Nuffield Health, all exercise professionals have experience working with clinical populations and work closely with clinical professionals on a daily basis within a shared learning environment.

Utilising the Nuffield Health accredited training academy, a multi-disciplinary team of clinical and exercise experts as well as experienced clinical operations specialists will deliver a comprehensive programme of training to up skill exercise professionals to COVID-19 rehabilitation specialists. At present no external standards exist regarding specific competencies in this area. The design of the programme and its content has however been carried out in collaboration with NHS representatives and key authorities from organisations leading rehabilitation nationally.

Training will be delivered via a blended learning approach utilising a mixture of interactive virtual classrooms, online learning, webinars and question and answer sessions. The content to be included covers:

An overview of the clinical impact of COVID-19, long term effects and the requirement for community rehabilitation and its goals.Roles and responsibilities of those involved in delivery of the rehabilitation programme.Physiotherapists will be refreshed on initial subjective assessment, screening for inclusion/exclusion and need for onward referral, use of outcome measures and handover process to ensure seamless patient journey.Exercise professionals cover week by week roles and responsibilities, systems training, outcome measures, red flags and escalation processes.Exercise professionals will further refresh and advance coaching skills, exercise programming, great conversations skills, exercise progression, and regression.All will receive mental Health First Aid training—recognising signs and symptoms of emotional distress and understanding how to signpost to appropriate treatment pathway.

All training will be assessed via formal assessment testing theoretical knowledge via online examination and practical skills assessed via role play scenarios and “course-work” tasks.

### Patient and Public Involvement

Patients were first involved in this evaluation at their point of clinical referral following a 12-week post discharge follow up. The research questions posed within the protocol paper were constructed with the support of NHS clinicians whom work directly with this clinical population as well-members of NHS Trust management. We believe that the research questions reflect the immediate and on-going needs of the NHS who have a strong insight as to their patient's needs.

Qualitative feedback will be collected from patients throughout their rehabilitation. An initial cohort of 100 patients will be invited to review each milestone of the programme as part of a focus group following their rehabilitation. An evaluation period will then be employed to refine the pathway based on patient feedback, this will include feedback on outcome and recruitment methods.

A patient survey will be provided to all participants that were eligible for the rehabilitation programme gauging views on the dissemination plan and how the intervention may further integrate into community settings.

## Measures

Outcome data will be collected at 0, 6, and 12 weeks and again at 6- and 12-months post-intervention. Self-report data will be collected via digital application (MyWellbeing, Nuffield Health, London, UK). The patient will be emailed and provided a push-notification prompting them to complete the aforementioned questionnaires. Whilst this evaluation will not utilise any formal comparison group, it is intended that collaboration with trusts will support the analysis of anonymised “usual care” outcome data. This is likely to come from community physiotherapy and/or modified pulmonary rehabilitation.

All data will be securely stored on a dedicated Nuffield Health server and will be retained in line with the organisations publicly available data retention schedule. Modifications to data written to the database will be documented through via an internal inquiry system. Data entered into the database will be retrievable for viewing throughout by those granted secure access privileges associated with an identification code and password. Any data errors will be summarised along with detailed descriptions for each specific problem in a data query reports, which will be sent to the study Outcomes Analyst. The Outcomes Analyst will check any inconsistency, checking other sources to determine required corrections. Any coding changes required within the digital data capture system will then be implemented within 24 h.

Complete back up of the primary database will be performed twice a month. Incremental data back-ups will be performed on a daily basis. In addition to system back-ups, additional measures will be taken to back-up and export the database on a regular basis at site level. The outcomes analyst will send weekly email reports with information on missing data, missing forms, and missing visits to site level co-ordinators who will then rectify immediately as and when required. Data security audits will be completed by the Nuffield Health Information Security group on a quarterly basis. Full details of group membership and details of audit processes can be provided upon request.

### Primary Outcome Measures

#### EuroQoL Five Dimension Five Level Version (EQ-5D-5 L)

This measure is used to assess a person's perception of their general health state and obtain a measure of quality adjusted life years (QALYs). Outcomes can be benchmarked against UK population norms. It covers five dimensions: mobility, self-care, usual activity, pain/discomfort and anxiety/depression, which are rated by the person on five levels of severity: no problems, slight problems, moderate problems, severe problems and extreme problems/unable to function within that domain (27).

### Dyspnea-12

Dyspnea-12 consists of 12 descriptor items on a scale of none (0), mild (1), moderate (2), or severe (3). It provides an overall score for breathlessness severity that incorporates seven physical items and five affective items. The time reference period for “these days” captures the current level of breathlessness experienced by patients as opposed to specifically on the day of the test or in response to a specific activity. Total scores range from 0 to 36, with higher scores corresponding to greater severity (28).

### Secondary Outcome Measures

#### Duke Activity Status Index

The Duke Activity Status Index (DASI) is an assessment tool used to evaluate the functional capacity of patients with cardio-pulmonary diseases (29). The activities in the scale are chosen to represent major aspects of physical function, i.e., personal care, ambulation, household tasks, sexual function, and recreational activities. As such, these responses can also be used to assess physical limitations relevant to the patient's HR-QoL. Responses from 12 items are summed up to get a total score, which ranges from 0 to 58.2. Higher scores indicate a higher functional capacity.

### 30 s Sit to Stand Test

The 30 s Sit to Stand Test is utilised for testing strength and endurance in a variety of cohorts. It is part of the Fullerton Functional Fitness Test Battery (30). This test was developed to overcome the floor effect of the 5 or 10 repetition sit to stand test in older adults. The 30-s chair stand involves recording the number of stands a person can complete in 30 s rather than the amount of time it takes to complete a pre-determined number of repetitions. That way, it is possible to assess a wide variety of ability levels with scores ranging from 0 for those who cannot complete 1 stand to > 20 for more fit individuals.

### Generalised Anxiety Disorder-7

GAD-7 comprises 7 items measuring symptoms and severity of anxiety based on the DSM-IV diagnostic criteria for GAD. The GAD-7 has good internal consistency (α = 0.92) and good convergent validity with other anxiety scales. Higher scores indicate greater severity of symptoms. The GAD-7 has increasingly been used in large-scale studies as a generic measure of change in anxiety symptomatology, using a cut-off score of 8 (31).

### Patient Health Questionnaire-9

The PHQ-9 is a self-report measure of depression that has been widely used in research and is a regular screening measure utilised in primary care and hospital settings. The PHQ-9 items reflect the diagnostic criteria for depression outlined by the Diagnostic and Statistical Manual of Mental Disorders, Fourth Edition—Text Revision (DSM–IV–TR) (32). Summary scores range from 0 to 27, where larger scores reflect a greater severity of depressive symptoms. The PHQ-9 has been found to discriminate well between depressed and non-depressed individuals using the cut-off total score ≥10, with good sensitivity (88.0%), specificity (88.0%) and reliability (33).

### Patient Experience and Programme Acceptability

The Patient Experience Questionnaire (PEQ) instrument will be used to assess patient experience and satisfaction. The PEQ contains several quantitative questions and open-ended questions that are used to assess participant's views and satisfaction with service provision (34).

### Costs

EQ-5D-5 L utilities will be reported alongside the full evaluation costs of the intervention so as to elicit a “per head” economic evaluation of all participants recruited (35).

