### Aims

The aim of the present evaluation is to implement and appraise a novel model of community rehabilitation for individuals recovering from COVID-19. The focus will be on the clinical effectiveness of the programme for improvements in HR-QoL and suppression of COVID-19 related symptoms. The specific research questions include the following:

Is HR-QoL improved and are symptoms related to COVID-19 reduced at 6 and 12 weeks post-intervention and are benefits retained at 6 and 12 months?Is a novel blended model (digital and physical) of care cost-effective in the rehabilitation of those recovering from COVID-19?Is a novel blended rehabilitation programme acceptable to both patients and rehabilitation specialists?

We hypothesise that: (a) the 12-week rehabilitation programme will be effective in improving HR-QoL and reducing symptoms related to COVID-19 at 6 and 12 weeks and those benefits will be retained at 6 and 12 months; (b) the blended model will be cost effective when compared to previously described rehabilitation methodologies, specifically outpatient multidisciplinary pulmonary rehabilitation; (c) we expect the programme to be acceptable to both patients and specialists.

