### Statistical Analysis

Participation levels will be monitored throughout the programme and reasons for withdrawal or non-compliance will be recorded. All participants are selected according to clinical criteria alone with no other factors influencing participation so as to limit selection bias. Information biases are limited via the prospective nature of this evaluation and the methodology employed to collect mandatory data at each designated time point. As well as the primary and secondary outcome measures being collected, a detailed clinical history and additional triage will be undertaken for each participant. This will limit confusion bias through the identification of relevant confounding clinical variables. Efficacy of treatments over time will be measured using mixed effects models. To complement the *post-hoc* comparisons, the magnitude of change on the primary and secondary outcomes measures will be established using Cohen's *d* statistic. Bonferroni corrected *p*-values will be reported for multiple comparisons. Participants with missing data will be removed for analysis with complete-case analysis being utilised.

An interim-analysis will be performed on the primary endpoint when 50% of participants have completed up to the 6-month follow up point. The interim analysis will be performed by an independent statistician. The statistician will report to the principal investigator ([name]) only. The principal investigator will have unblinded access to all data and will discuss the results of the interim analysis with the project team.

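### Costs are promised for everyone recruited, but the missing-data rule leaves utilities only for complete cases, so the two sides of the economic result would describe different people

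*Protocol article*

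**What the plan says.** The Costs section says that "EQ-5D-5 L utilities will be reported alongside the full evaluation costs of the intervention", to give a per-head "economic evaluation of all participants recruited". The section on the EQ-5D-5L makes that instrument both a primary outcome and the source of QALYs.

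The Statistical Analysis section says: "Participants with missing data will be removed for analysis with complete-case analysis being utilised". The sentence is not limited to particular outcomes and does not exempt the economic analysis.

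The Measures section sets five collection points: "Outcome data will be collected at 0, 6, and 12 weeks and again at 6- and 12-months post-intervention". The forms are completed by the patient through an app, after email and push prompts.

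Cost-effectiveness is a stated aim. Hypothesis (b) under Aims is that "the blended model will be cost effective when compared to previously described rehabilitation methodologies", with outpatient pulmonary rehabilitation named as the reference. The abstract lists QALYs among the secondary outcomes.

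**The concern.** The two rules name different populations. The Costs section refers to everyone recruited, whereas the Statistical Analysis section keeps only people without missing data. Because the EQ-5D-5L is a primary outcome, the complete-case rule covers it on its face. The utilities set beside the costs would then come from a selected subset.

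This is a conflict between two things the article does fix, not a detail left open. A fuller analysis plan could not honour both without changing one of them.

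A cost-effectiveness statement needs both quantities for the same people. If complete cases do better than those removed, their average gain is credited to a cost that was spent on everyone. Individual cost also varies: a patient whose progress is judged insufficient at the mid-point review is advised differently from the rest, in that "the patient will be recommended to complete another 6-week digital programme in full". It therefore matters which people are counted on the cost side as well.

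**Working it through.** The article states no cost, QALY, withdrawal or cost-per-QALY figure, so there is nothing to reproduce. The steps below show what its rules imply under assumed inputs.

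**Step 1: how many would be complete cases.** From the documents: a cohort of at most 160 (Trial Design), and a baseline plus four follow-ups (Measures). Assumed: baseline complete, and each follow-up missing independently with probability m. The complete share is p = (1 − m)^4.

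| m (assumed) | p | complete of 160 |
|---|---|---|
| 0.05 | 0.815 | 130 |
| 0.10 | 0.656 | 105 |
| 0.15 | 0.522 | 84 |
| 0.20 | 0.410 | 66 |

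Modest loss at each visit is enough to bring p into the range 0.6 to 0.8 used below.

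**Step 2: the reference value.** Set the cost and the QALY gain of a complete case to 1. Let c and g be the cost and gain of a removed participant relative to that. With everyone on both sides, cost per QALY is

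[p + (1 − p)c] / [p + (1 − p)g].

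**Step 3: three ways of combining the stated rules, each divided by the reference.**

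- **A.** Mean cost over all recruited, divided by mean gain in complete cases: the factor is p + (1 − p)g.
- **B.** Both from complete cases: the factor is [p + (1 − p)g] / [p + (1 − p)c].
- **C.** Total cost of all recruited, divided by QALYs summed over complete cases only: the factor is [p + (1 − p)g] / p.

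**Step 4: results for A.**

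| p | g = 0 | g = 0.5 | g = 1 | g = 1.2 |
|---|---|---|---|---|
| 0.8 | 0.80 | 0.90 | 1.00 | 1.04 |
| 0.7 | 0.70 | 0.85 | 1.00 | 1.06 |
| 0.6 | 0.60 | 0.80 | 1.00 | 1.08 |

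For example, 0.8 + 0.2 × 0.5 = 0.90, and 0.6 + 0.4 × 0 = 0.60. The factor contains no c. Averaging cost over everyone is correct for an all-recruited result, so the relative cost of those removed cancels. The error lies entirely in the selection of utilities.

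**Step 5: results for B and C at p = 0.7.**

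- B runs from 0.70 (c = 1, g = 0) to 1.06 / 0.775 = 1.37 (c = 0.25, g = 1.2).
- C is 0.70 / 0.70 = 1.00 at g = 0, 0.85 / 0.70 = 1.21 at g = 0.5, 1.00 / 0.70 = 1.43 at g = 1 and 1.06 / 0.70 = 1.51 at g = 1.2. Over these values the programme never looks cheaper than it is.

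**The case against.** The strongest reply is that no direction of bias can be read from the article. It gives no formula for cost per QALY; utilities are only to be reported beside costs. It does not say how the two are combined or how those removed compare with those kept. Under C the programme looks dearer, or unchanged if those removed gain nothing, and under B the result can go either way. This stands, and it limits the size claim to a conditional one. It does not remove the conflict over populations, and hypothesis (b) still needs costs and QALYs to be brought together.

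A reader might infer that people who stop early make the programme look cheap by lowering the average cost. The algebra does not support this: under A the relative cost drops out. Nor is missing data the same as stopping early. Someone who finishes the 12 weeks and skips one later questionnaire is also removed, and may have gained fully.

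A reader might also count patients who withhold their data as cost without benefit, since "The patient may also request that their data is not utilised and will still be able to participate in the programme". The article does not say that they enter the evaluation cohort or its cost denominator, and they may well be service users outside it. Likewise, nothing states how deaths are handled in the economic analysis, so a claim that they are deleted as missing would be inference.

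Finally, it may be said that this is only the general complete-case problem again. The source of bias is indeed the same. What is particular here is the express promise of an all-recruited basis, which the missing-data rule prevents.

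**Conclusion.** The point holds as a conflict of populations. The Costs section and the complete-case rule cannot both be followed without pairing the cost of everyone recruited with the utilities of a subset. The issue bears on a stated aim and should be settled before analysis.

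The size is conditional. Under reading A, with assumed p of 0.6 to 0.8 and g of 0 to 0.5, cost per QALY would be 0.60 to 0.90 of its all-recruited value, an understatement of 10% to 40%. If gains are equal there is no bias. If those removed gain more, or if total cost is divided by QALYs summed over complete cases with some positive gain among those removed, cost per QALY is overstated. The article supports neither a general claim that the programme will look cheaper nor an attribution to early stopping.

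**What to change.** Reconcile the Costs and Statistical Analysis sections as follows.

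- **One population for costs and QALYs:** all who start the programme and permit use of their data.
- **Costs:** as incurred in that population, including any repeated digital phase and any early stopping.
- **QALYs:** all observed EQ-5D-5L values, with multiple imputation of missing ones, stated as an exception to the complete-case rule.
- **Sensitivity analysis:** complete cases, with both costs and QALYs restricted to them.

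If this is not done, the Costs section should no longer claim to cover everyone recruited.

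The change costs some wording and modest extra analysis, and may give a less favourable economic result. Person-level costing is not assured: the Engagement and Usage Measures section describes the platform data as anonymised and counts a session as a log-on, not a delivered class or call. If those data cannot be linked to individuals, use an average cost over the same population.
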